## Abstract

**Background:**

Childhood overweight has noticeable psychological and social consequences for the child and leads to an increased risk of mortality and morbidity later in life. With the high prevalence of overweight in children and adolescents, it is important to identify effective approaches for the prevention and treatment of overweight in children and young individuals. The primary aim of the study is to assess the effect of an intensive day-camp intervention on body mass index (BMI) in overweight children.

**Methods:**

The Odense Overweight Intervention Study is a semi-blinded randomized controlled trial. Overweight children from the Municipality of Odense, Denmark, were invited to participate in the trial. Based on power calculations 98 participants were found to be sufficient to randomize in order to find an effect of minimum 1.5 BMI points. Gender-stratified concealed block randomization with a ratio of 1:1 and random block sizes of two, four, and six ensured balance between study arms. The intervention consisted of a six-week multi-component day camp including increased physical activity, healthy diet and health education followed by 46 weeks of family-based habitual intervention. The standard care arm was offered two weekly hours of physical activity training for six weeks. The outcomes were measured at baseline and at six-week and 52-week follow-ups. Furthermore, BMI will be assessed again at 48-month follow-up. Test personnel were kept blinded. The intervention effect will be evaluated using mixed model analyses. During 2012 and 2013, 115 children were enrolled in the study. Fifty-nine children were randomized to the day-camp intervention arm and 56 to the standard intervention arm.

**Discussion:**

This study will provide novel information about the long-term health effects of an intense day-camp intervention program on overweight children, due to the design and the follow-up period. Moreover, it will add to the knowledge on designing and implementing feasible camp settings for preventing overweight in children.

**Trial registration:**

NCT01574352 at http://clinicaltrials.gov on the 8th of March 2012.

## Background

Strong and consistent evidence has shown that overweight, including obesity, is a significant risk factor for the development of cardiovascular disease (CVD) in adults [1,2]. Several studies have found an association between overweight in childhood and increased risk of morbidity and mortality later in life [3-5]. Considering the high prevalence of overweight in children and adolescents, it is crucial to identify effective approaches for the prevention and treatment of overweight in children and young individuals [6,7]. According to a Cochrane review and meta-analysis from 2009, very few well-designed randomized controlled trials (RCT) have been conducted on the reversal of overweight in childhood and adolescence [8]. Of these studies, treatment strategies with the highest efficacy included combined diet, physical activity and other lifestyle interventions in both outpatient clinics and public school settings. Drug therapy showed an effect as well; however, these generally cause a range of adverse effects. Thus, drug therapy can be considered unsuitable to treat overweight in otherwise healthy children. When targeting prepubescent children, family involvement has been shown to be particularly effective [8]. Most studies conducted suffer from a lack of quality, such as low statistical power, high dropout, unadjusted outcome measures, and a relatively short follow-up time (<12 months). Consequently, well-designed high-quality studies are still needed on the reversal of overweight in childhood with increased focus on documenting predictors of behavior changes associated with clinical decreases in overweight. Approaches such as resident weight-loss camps have shown promising results [9-18]. A residential camp setting provides an opportunity to control exposure to, for instance, particular foodstuffs, beverages and physical activity opportunities. Some studies have shown a noticeable effect on body mass index (BMI) and other CVD risk factors after camp stays as short as two weeks. Generally, longer camp stays tend to be related to more pronounced effects [9,13,15]. However, little is yet known about the long-term effects of the residential camp approach. Gately et al. observed a decreased BMI in participants after an eight-week camp-based intervention program, both in the short term and at a ten-month follow-up [10]. Nonetheless, this study was uncontrolled and offered no intervention in the follow-up period. In a semi-controlled design, Nowicka et al. studied the effect of a 1-week resident sports camp with six months of supported follow-up intervention. They found no effect on overweight status after 12 months [16]. The short duration of the camp may explain the result. In an eight-week summer camp setting for overweight adolescents, Southam et al. invited parents to weekly meetings to discuss the program content, thereby involving parents more actively in changing the habits of their children. Despite significant effects observed at completion of the camp, no follow-up assessments were performed [13]. Thus, well-designed RCT with longer follow-up periods also involving the parents are needed to test whether an approach in which children are invited to stay at a camp setting, away from their everyday environment, can be effective in prevention of overweight. Earlier experiences with camps for overweight children in the municipality of Odense, Denmark, have shown promising results. Since 2005, the municipality has offered overweight fifth-grade children a six-week stay on a remote camp location, Fanoe Island, and a consecutive family-focused intervention (*Camp Fanoe*). Experiences from Camp Fanoe demonstrate that some children choose not to participate because of the distance and the six-week period away from their family [19]. Furthermore, the promising results potentially can be transferred to other settings. As a result the Odense Overweight Intervention Study (OOIS) was developed as a RCT, based on the framework and experiences from Camp Fanoe. However, the camp was moved to the center of the city of Odense (the third largest city in Denmark) and designed as a day camp instead of a residential camp.

### Study aims and hypothesis

The main purpose of the OOIS is to test the effect on BMI in a group of 11- to 13-year-old overweight and obese children participating in a one-year multi-component modified camp approach. The secondary aims of the study are to assess the intervention’s effect on CVD risk factors, cognitive skills, and motor skills. Furthermore, we aim to investigate the development of BMI four years subsequent to the initialization of the study. Our hypothesis is that the approach will induce a reduction of overweight in the intervention group compared to the control group over a one-year period. We aim to translate the research findings into intervention products and guidelines usable in practice in both national and international programs on prevention of overweight among children and youth. The primary aim of this paper is to describe the design and the study protocol of the OOIS.

## Methods

### Study design

The OOIS is a semi-blinded randomized controlled trial (RCT) with four measurement occasions. A population-based sample of overweight and obese children were invited to participate in either an already established resident overweight camp (Camp Fanoe) or the RCT. The participants choosing the RCT were randomly allocated to either the Day Camp Intervention Arm (DCIA) or the Standard Intervention Arm (SIA). The DCIA is a day camp lasting six weeks with a subsequent 46-week follow-up parent-supported intervention period. The SIA is a standard physical activity intervention consisting of one weekly activity class for six consecutive weeks.

### Recruitment and eligibility criteria

Approximately 4400 children from the municipality of Odense were invited to the mandatory annual schoolchild examinations in fifth grade from September to December 2011 and from September to December 2012. The children’s height, weight, and waist circumferences were measured by school health nurses. If participants exceeded age- and sex-specific BMI cut-points for overweight defined according to the International Obesity Task Force [20], they were informed about the two existing possibilities: the OOIS or Camp Fanoe. Criteria for exclusion from the OOIS were:

1. The child participated in other intervention research involving cardiovascular risk management.

2. The child did not attend a regular school or was attending a special class (“OBS” class), typically due to behavioral issues.

3. The child had a known endogenous cause of overweight.

4. The child had a motor-control handicap which hindered normal participation in physical activity.

5. The child had known violent behavior.

### Ethics and trial registration

Before initializing the study, the study protocol was approved by The Regional Scientific Ethical Committee for Southern Denmark (Approval number: S-20120015), registered with the Danish Data Protection Agency and at ClinicalTrial.gov (Registration number: NCT01574352). Written informed consent from children and their parents or legal guardians were obtained. Twice during the study the participants received parts of their personal results to keep them updated about their progression. The first of these was received after the first follow-up measurement and the second after the third follow-up.

### Sample size and randomization

It was expected that approximately 330 (15%) of a total of approximately 2200 fifth-grade children each school year would fulfill the eligibility criteria. Based on earlier experience we estimated that around 160 children would be interested in participating in the OOIS and/or Camp Fanoe. Each year Camp Fanoe enrolls 40 participants, which potentially leaves approximately 120 participants to choose the OOIS. During 2011–2012, 65 children were enrolled in the study, and during 2012–2013, an additional 50 participants were enrolled. Based on previous experiences from Camp Fanoe [19] and a pilot day camp conducted in 2011, a minimum difference of 1.5 BMI points (2.3 SD) between the DCIA and the SIA over 12 months was expected. Thus, 37 participants in each intervention arm were needed to achieve a power (1 - β) of 80% to find a significant difference between the intervention and control group (two-sided, α = 0.05) on the primary outcome (BMI). With an expected 30% attrition, 49 participants in each arm were to be recruited (total N = 98). To reduce attrition during the trial, children received a small gift (movie tickets) for participation at the three measurement occasions. Participation in either of the interventions was free of charge. Gender-stratified concealed block randomization with a ratio of 1:1 and a block size of two, four, and six (random permuted blocks) ensured balance between intervention arms. The randomization was generated using the web-based software http://www.randomization.com and http://www.random.org (flow of participants until spring 2013 is presented in Figure 1).

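### The 30% attrition allowance was added to 37 per arm instead of dividing by 0.70, so 98 children do not give the stated 80% power

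*Protocol article*

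**What the plan says.** The protocol article, under Sample size and randomization, sets out the calculation in three steps.

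- **Effect:** "a minimum difference of 1.5 BMI points (2.3 SD) between the DCIA and the SIA over 12 months was expected".
- **Evaluable number:** "37 participants in each intervention arm were needed to achieve a power" of 80%, with the test specified as "two-sided, α = 0.05" and BMI as the primary outcome.
- **Allowance for loss:** "With an expected 30% attrition, 49 participants in each arm were to be recruited", 98 in total.

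The Methods part of the abstract carries the result forward without the attrition rate: "Based on power calculations 98 participants were found to be sufficient to randomize". It also reports actual enrolment of 115 children, 59 in the day-camp arm and 56 in the standard arm. The article gives no other attrition rate or inflation rule.

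**The concern.** An attrition allowance should leave the required number of evaluable children after the expected losses. Here the required number is 37 per arm, the expected loss is 30%, and the recruitment figure is 49 per arm. Taking 30% from 49 does not leave 37.

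The figure at stake is the trial's headline sample size. If it is wrong, the claim that 98 randomised children suffice for 80% power fails on the plan's own assumptions, and the error would pass into the results report, which the plan says will follow CONSORT.

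**Working it through.** **Inputs, all from Sample size and randomization unless noted**

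- Difference to detect: 1.5 BMI points
- SD: 2.3 BMI points (an interpretation, tested in step 1)
- Two-sided α = 0.05, power 80%, allocation 1:1
- Evaluable number: 37 per arm
- Attrition: 30%
- Stated recruitment: 49 per arm, 98 in total
- Actual enrolment: 59 and 56 (abstract)

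**Step 1. Reproduce the 37.** The normal-approximation formula for two means is

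n per arm = 2 × (z₀.₉₇₅ + z₀.₈₀)² × (SD/δ)² = 2 × (1.960 + 0.842)² × (2.3/1.5)² = 36.9, so 37.

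Power at 37 per arm is 80.1%, so the plan's figure reproduces. Reading 2.3 as a standardised effect would need only 3 per arm, and a one-sided test would need 30. Neither gives 37, so SD = 2.3 is the reading to use.

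**Step 2. Reproduce the 49.**

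| Rule | Calculation | Per arm | Total |
|---|---|---|---|
| Multiply by (1 + 0.30) | 37 × 1.30 = 48.1 | 49 | 98 |
| Divide by (1 − 0.30) | 37 / 0.70 = 52.9 | 53 | 106 |

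Only the first rule returns the stated 49.

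**Step 3. Check what each target retains.**

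- 49 × 0.70 = 34.3 per arm, which is 2.7 short of 37.
- 53 × 0.70 = 37.1 per arm, which is enough.
- 49 per arm keeps 37 only if attrition is at most 1 − 37/49 = 24.5%.

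**Step 4. Power.** By the normal approximation, power = Φ(δ / (SD × √(2/n)) − 1.960). The t-test figures use the noncentral t distribution.

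| Evaluable per arm | Normal approximation | t-test |
|---|---|---|
| 37 (required) | 80.1% | 79.0% |
| 34.3 (49 less 30%) | 77.1% | 75.9% |
| 34 (rounded down) | 76.7% | 75.5% |
| 41.3 and 39.2 (59 and 56 less 30%) | 83.3% | 82.4% |
| 41 and 39 (rounded) | 83.0% | 82.1% |

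Compared on the same basis, the slip costs 80.1 − 77.1 = 3.0 points (normal) or 79.0 − 75.9 = 3.1 points (t-test).

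**Step 5. Actual enrolment.** 115 exceeds 106. The smaller arm of 56 keeps 37 as long as attrition is at most 1 − 37/56 = 33.9%.

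**The case against.** The strongest reply is that the error has no practical consequence. Enrolment is complete at 115, above the corrected 106, and power at 30% attrition is above 80%. That is right for the trial as run, and it limits the matter to the stated justification. It does not make the statement about 98 correct.

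Four further points deserve an answer.

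- **Basis of the power figure.** The 37 is a normal-approximation number, and on the t-test 37 per arm already gives 79.0%. Setting a t-test figure of 75.5% against 80% therefore charges the attrition step with about a point that it did not cause, and rounding 34.3 down to 34 adds a little more. This stands: the loss due to attrition is about 3 points.
- **The SD is an inference.** The notation for the SD is ambiguous, so the power figures depend on an interpretation. This also stands, although that interpretation is the one that returns 37. The step from 37 to 49 or 53 does not use the SD at all.
- **The abstract gives no attrition rate.** Taken alone, 98 is enough for attrition up to 24.5%. But the abstract reports the result of the calculation in the methods, and that calculation assumes 30%.
- **Mixed models use partial data.** BMI is also measured at baseline and six weeks, so children lost before 12 months may contribute something. The sample size paragraph takes no credit for this. It counts lost children as lost, which is why it inflates.

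**Conclusion.** The concern holds. The article's 37, 30% and 49 are incompatible. With 37 evaluable children needed per arm and 30% attrition, the target is 53 per arm and 106 in total, so the stated 98 is 8 children short. At 98, power is about 77% by the normal approximation the plan evidently used, or about 76% by the t-test, against the stated 80%.

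The recruitment shortfall rests only on the printed 37 and 30%. The power figures also assume an SD of 2.3 BMI points, and that children who drop out contribute nothing at 12 months, as the plan's own allowance does. The error is modest in size and lies in the justification. Under the same assumptions, the 115 enrolled retain more than 80% power at 30% attrition.

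**What to change.** Correct the statement under Sample size and randomization and in the abstract. Because the text reports a target that was set in the past and enrolment has closed, the clearest form is to:

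1. keep 49 per arm (98) as the target that was set at the time;
2. state that 37 evaluable per arm with 30% attrition requires 37 / 0.70, that is 53 per arm and 106 in total;
3. give the power of 98 at 30% attrition as about 77% (normal approximation) or 76% (t-test), naming the basis;
4. state that 115 were enrolled, which gives about 82% to 83% power at 30% attrition;
5. write the SD explicitly as 2.3 BMI points, if that is what was meant, so that the 37 can be checked.

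If the historical target need not be preserved, replacing 49 and 98 with 53 and 106 in both places is sufficient. In the abstract, 98 should no longer be called sufficient without qualification.

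The cost is wording only. No recruitment, analysis or endpoint changes. The original target simply looks slightly less favourable.

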**Figure 1 F1:**
[figure not shown]
Diagram of preliminary participant flow.

### Blinding and allocation concealment

Researchers were blinded at all assessments except for the ultrasonographer, due to his prior knowledge of the participants. The ultrasonographer was not involved in any other measurement procedures. Due to consideration for the participating families, and to avoid additional dropout on this account, it was necessary to inform participants of allocation three weeks prior to baseline measurements. Thus, allocation concealment was not possible.

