**Motor skills and fitness**					
Manual dexterity, aiming and catching, and balance	The objective part of the Movement-ABC II test battery was applied.	√		√	√
Hand grip strength	Hand grip strength was assessed using a Smedley Dynamometer (max. 100 kg).	√		√	√
Jump height	Jump height was assessed by measuring tape using the Sargent jump protocol. The best of three jumps was noted.	√		√	√
Cardiorespiratory fitness	Cardiorespiratory fitness was assessed using a progressive bicycle ergometer protocol (Monarch Ergomedic 839e) until total exhaustion with indirect calorimetry (Innovision, AMIS 2001) and a Polar RS800CX heart rate monitor.	√		√	√
Arterial health	Blood pressure was assessed on the left upper arm with an automatic blood pressure monitor (Welch Allyn 300 series) after 5 minutes of rest in a sitting position. Resting heart rate was assessed by heart rate monitor (Polar RS800CX) during the ultrasound assessment as the child already was in a horizontal position and relaxed. Intima-media thickness and carotid elasticity were assessed in a lateral and a posterior position on the carotid artery with a GE LOGIQ e portable ultrasound machine with an attached 12 L-RS probe.	√		√	√
**Blood measurements**	After an overnight fast, blood samples were drawn in the morning from the antecubital vein (right arm). Participants were lying supine during blood collection. Samples for serum were left at room temperature for 30 minutes. Samples for plasma (EDTA) were centrifuged as soon as possible and put in the icebox (within one hour) before centrifugation. All samples were centrifuged at 2500G for 10 minutes. Then the samples were stored at -80°C until analysis.				
CVD risk factors	Fasting blood samples were analyzed for insulin, glucose, HbA1c, and lipids.	√		√	√
Growth factors	Fasting blood samples were analyzed for BDNF and FGF-21.	√		√	√
Adipokines and myokines	Fasting blood samples were analyzed for leptin, adiponectin, and irisin.	√		√	√
Inflammatory factors	Fasting blood samples were analyzed for CRP, TNF-α, and IL-6.	√		√	√
**Cognitive function**	The testing environment was comfortable and free from distraction. The cognitive tasks were administered individually in the following order:				
Visual memory	Rey Complex Figure Test (RCFT)	√		√	√
Attention and processing speed	Symbol Digit Modalities Test (SDMT)	√		√	√
Attention and executive function	Trail Making Test A & B (TMT A & B)	√		√	√
Executive function	Stroop Color and Word Test	√		√	√

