### Outcomes

The screening process for overweight was performed by school nurses by assessing height and weight, thus making it relevant to use BMI as the primary outcome. Moreover, BMI and BMI z-score are frequently used as primary outcomes in comparable overweight interventions. To complement and validate the BMI assessment, body composition by DEXA scanning will be introduced. Furthermore, as a secondary outcome, a modified composite metabolic risk z-score will be calculated based on the definition by Andersen et al. [24]. This modified version contains summed z-scores for systolic blood pressure, triglycerides, total cholesterol/HDL ratio, insulin resistance (HOMA-IR), abdominal fatness by waist circumference, and aerobic fitness.

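### The abstract says test personnel were blinded without exception, but the carotid ultrasound outcomes were acquired by an unblinded operator at all three visits

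*Protocol article*

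**What the plan says.** The protocol article makes three statements that bear on this point.

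- **Abstract, Methods.** The design is introduced as semi-blinded: "The Odense Overweight Intervention Study is a semi-blinded randomized controlled trial". Further on, the abstract says "Test personnel were kept blinded", with no exception.
- **Methods, Blinding and allocation concealment.** "Researchers were blinded at all assessments except for the ultrasonographer, due to his prior knowledge of the participants". The next sentence limits his role: "The ultrasonographer was not involved in any other measurement procedures". The same section says that families learned their allocation three weeks before the baseline measurements.
- **Table 1, Arterial health.** "Intima-media thickness and carotid elasticity were assessed in a lateral and a posterior position on the carotid artery", using a portable ultrasound machine. The row is ticked at baseline, post camp and post intervention.

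The article does not say whether the images are stored, who measures them, or whether the person measuring knows the arm or visit.

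**The concern.** Blinding of assessors is the main protection in a trial whose families necessarily know their arm. For the carotid measures that protection is absent at acquisition, because the person holding the probe is the one assessor declared unblinded. If his expectations affected what was recorded, the result could be a between-arm difference in intima-media thickness or elasticity that is not an effect of the intervention. A reader who sees only the abstract would not know that these outcomes differ from the rest in this respect.

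**Working it through.** **1. The statements side by side.**

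| Place | Who was blinded | Exception |
|---|---|---|
| Abstract, Methods | Test personnel | None given |
| Blinding and allocation concealment | Researchers, at all assessments | The ultrasonographer |

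The ultrasonographer carries out an assessment, so he belongs to the test personnel. The two statements cannot both be true as worded. The Methods section is the specific one and gives a reason, so the abstract sentence is the one to qualify.

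**2. Which outcomes are exposed.** Table 1 ties ultrasound to two outcomes, carotid intima-media thickness and carotid elasticity, at three time points.

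**3. Whether baseline is protected.** It cannot be assumed to be. Families knew their allocation three weeks before baseline, and the section on additional data collection describes baseline as post-randomization. No carotid value predates allocation, so adjusting for the baseline value cannot be relied on to remove an operator effect.

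**4. Which outcomes are not exposed.** The Outcomes section bases the primary outcome on height and weight: "thus making it relevant to use BMI as the primary outcome". The composite secondary score sums six parts: systolic blood pressure, two lipid terms, HOMA-IR, waist circumference and fitness. None is a carotid measure. The ultrasonographer took no other measurements.

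**5. Size.** The plan gives no figure for assessor bias, so the following is illustration only, on an assumed range.

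- Number per arm: the plan's 37, calculated for BMI. It reproduces when 2.3 is read as the SD in BMI points: n = 2 × (1.960 + 0.842)² × 2.3² / 1.5² = 36.9, rounded up to 37, with power 80.1%. The number of children with usable carotid scans is not stated.
- Assumed systematic shift between arms, b, in SD units: 0.1 to 0.3.
- Standard error of the difference in SD units: √(2/37) = 0.2325.
- Chance of a two-sided 5% significant result with no true effect: 1 − Φ(1.960 − b/0.2325) + Φ(−1.960 − b/0.2325).

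| Assumed shift b (SD) | b / 0.2325 | False-positive rate |
|---|---|---|
| 0 | 0 | 5.0% |
| 0.1 | 0.43 | 7.1% |
| 0.2 | 0.86 | 13.8% |
| 0.3 | 1.29 | 25.2% |

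The table shows only that a fairly small shift would matter. It is not evidence that a shift occurred.

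**The case against.** The strongest reply is that the limitation is disclosed and contained. The Methods section names the exception, gives the reason and keeps this operator away from every other measurement. The abstract also calls the trial semi-blinded. Disclosure in the Methods does stand, and it protects the other outcomes. It does nothing for the carotid outcomes themselves. The label semi-blinded is not defined, and it fits equally well a trial with unblinded families and fully blinded assessors, which is what the abstract's later sentence suggests.

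The importance is also open to challenge. Table 1 uses the heading for CVD risk factors for blood analytes and lists the carotid measures separately under arterial health. Counting them under the secondary aim on CVD risk factors is therefore a reasonable inference, not something the article states. This keeps the point modest.

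Three stronger readings are tempting, and the documents do not support them.

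- **That the scans were also read unblinded.** The article is silent on reading, and an article may leave this to the full protocol. Only unblinded acquisition is established.
- **That coded reading would largely remove the bias.** Coding blinds only the later measurement. Whatever was decided while scanning stays with the unblinded operator.
- **That resting heart rate is compromised too, or contradicts the statement limiting his role.** Table 1 says: "Resting heart rate was assessed by heart rate monitor (Polar RS800CX) during the ultrasound assessment". The value comes from a monitor, and nothing says that the ultrasonographer recorded it. Sharing a session is not a contradiction.

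**Conclusion.** The point holds in a limited form. The abstract claims blinded test personnel without exception, and the Methods section contradicts this for one assessor. Carotid intima-media thickness and carotid elasticity were therefore acquired unblinded at baseline, six weeks and 52 weeks. The bias cannot be sized from the documents. BMI and the composite metabolic risk score are unaffected. This calls for a correction of wording and a sensible safeguard for two non-primary outcomes; it does not threaten the main conclusion of the trial. The verdict rests on taking the blinding section at its word and on Table 1's attribution of both measures to ultrasound. It assumes nothing about how the images are read.

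**What to change.** 1. In the abstract, say that test personnel other than the ultrasonographer were blinded.
2. State whether the scans are stored and whether they are read without knowledge of arm and visit.
3. Where scans are stored and not already read blind, code them without name, arm or visit. Have the existing operator measure them in one batch, in random order, after the last 52-week visit. The article places the last measurements in spring 2014, still ahead when it was written, so this was still possible.
4. Report both carotid outcomes as unblinded at acquisition, and label any value that cannot be re-read from a stored image as unblinded.

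The cost is a few words in the abstract and, if images are retrievable, file coding and one batch reading, with no extra visits. Carotid results would arrive later. Some bias can remain because acquisition stays unblinded. If images were not stored, only the wording and labelling changes are available.
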